## Abstract

**Background:**

Surgical site infections (SSI) complicate up to 40% of surgical procedures, leading to increased patient morbidity and mortality. Previous research identified disparities in SSI prevention guidelines and clinical practices across different institutions. The study aims to identify variations in SSI prevention practices within and between specialties and financial systems and provide a representation of existing SSI preventative measures to help improve the standardization of SSI prevention practices.

**Methods:**

This collaborative cross-sectional survey will be aimed at pan-surgical specialties internationally. The study has been designed and will be reported in line with the CROSS and CHERRIES standards. An international study steering committee will design and internally validate the survey in multiple consensus-based rounds. This will be based on SSI prevention measures outlined in the CDC (2017), WHO (2018), NICE (2019), Wounds UK (2020) and the International Surgical Wound Complications Advisory Panel (ISWCAP) guidelines. The questionnaire will include demographics, SSI surveillance, preoperative, peri-operative and postoperative SSI prevention. Data will be collected on participants' surgical specialty, operative grade, of practice and financial healthcare system of practice. The online survey will be designed and disseminated using Qualtrics^XM^ Platform™ through national and international surgical colleges and societies, in addition to social media and snowballing. Data collection will be open for 3 months with reminders, and raking will be used to ascertain the sample. Responses will be analyzed, and the chi-square test used to evaluate the impact of SSI prevention variables on responses.

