### Objectives

2.1.

Primary objective:
-To identify the barriers to establishing standardized SSI prevention practice.Secondary objectives:
-To identify intra- and inter-specialty variations in surgical site infection prevention practice.-To identify variations in practice amongst financial systems such as state and privately funded healthcare systems and economical classifications.

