### Sample characteristics

2.4.

The survey will be sent out electronically to surgeons of any specialty and at all levels of training worldwide. This includes consultants, and surgical trainees (specialties registrars/residents). To be included in the study, surgeons must be currently practicing and be registered with the national surgical body/college/society. The validated online survey will be distributed through Qualtrics^XM^ for single-stage cluster sampling in addition to dissemination through social media, where snowballing may occur. Each network of distribution will provide a cluster, i.e., VERN for the vascular surgeons and PIACO group for general surgery. The study population will provide a representation of existing SSI preventative measures used worldwide.

Given the global nature of the survey, no sample size will be calculated. Raking will be used to assign weight values to each survey respondent in such a manner, that the weighted distribution of the sample is in very close agreement with two or more marginal control variables. Socio-economic (developing vs. developed countries) variables and surgical specialties will be used to weigh the sample of responses. As such, results will be able to be extrapolated into wider populations, irrespective of the distribution of responses received.

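### The only test named is an unqualified chi-square, for data that will be raked and sampled in clusters; run as an ordinary chi-square it would generally give p-values that are too small

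*Protocol article*

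**What the plan says.** The Methods paragraph of the abstract says that replies will be analysed with "the chi-square test used to evaluate the impact of SSI prevention variables on responses". No other test is named in the article, and the type of chi-square is not given.

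Section 2.4 (Sample characteristics) fixes the design:

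- **Weights.** "Raking will be used to assign weight values to each survey respondent". The margins are two: "Socio-economic (developing vs. developed countries) variables and surgical specialties will be used to weigh the sample of responses". The weighted results are meant to carry over to wider populations whatever mix of replies arrives.
- **Clusters.** The survey is distributed "for single-stage cluster sampling in addition to dissemination through social media, where snowballing may occur". "Each network of distribution will provide a cluster", and the two examples given, VERN and PIACO, each serve one specialty.
- **Size.** "no sample size will be calculated", so no number or size of clusters is stated.

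Section 2.1 (Objectives) lists as a secondary objective "To identify intra- and inter-specialty variations in surgical site infection prevention practice". Variation between financial systems and economic classes is the other secondary objective. The primary objective concerns barriers to standardised practice.

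**The concern.** The usual chi-square compares observed with expected counts on the footing that every reply is independent and counts once. The stated design departs from both conditions. Raking makes some replies count for more than others. Surgeons reached through the same network may also answer more alike than surgeons drawn at random. If either feature is ignored, the test credits the data with more information than they hold.

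Comparisons between specialties are the most exposed. If each network serves one specialty, as both examples do, a specialty contrast is largely a contrast between whole clusters, and that is where within-cluster correlation does most harm. At stake is how often the survey would report a difference in practice between specialties or financial systems that is only sampling noise. Leaving the weights out of the test avoids the weighting problem, but the test would then address something other than the weighted percentages that section 2.4 intends to generalise.

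**Working it through.** The article gives no significance level, intraclass correlation (ICC), cluster size or spread of weights, so there is no figure of its own to reproduce. Everything below rests on assumed inputs, with a nominal level of 5%.

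**Step 1: from design effect to true error.** If the variance is inflated by a design effect *deff* that the test ignores, the true type I error is P(χ²_df > c/deff), where c is the 5% critical value. For 1 df, c = 3.841.

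| Assumed deff | c/deff | True error, 1 df |
|---|---|---|
| 1 | 3.841 | 5.0% |
| 1.0625 | 3.615 | 5.7% |
| 1.5 | 2.561 | 11.0% |
| 2 | 1.921 | 16.6% |
| 3 | 1.280 | 25.8% |

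The error rate doubles to 10% at a deff of about 1.42 and triples to 15% at about 1.85.

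**Step 2: what weighting could contribute.** The Kish approximation is deff = 1 + CV² of the weights. For one margin with reply shares r and target shares t, it equals Σ t²/r. It depends on the population target as well as on the replies. With replies assumed to split 80/20:

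- target 70/30: 0.49/0.8 + 0.09/0.2 = 1.06
- target 50/50: 0.25/0.8 + 0.25/0.2 = 1.56
- target 40/60: 0.16/0.8 + 0.36/0.2 = 2.00

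This inflation applies only if the weighted counts are entered into the test as if they were real counts.

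**Step 3: what clustering could contribute.** When whole clusters of size m are compared, deff = 1 + (m − 1) × ICC.

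| m | ICC | deff | True error, 1 df |
|---|---|---|---|
| 10 | 0.01 | 1.09 | 6.0% |
| 50 | 0.01 | 1.49 | 10.8% |
| 100 | 0.02 | 2.98 | 25.6% |
| 50 | 0.05 | 3.45 | 29.1% |

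**Step 4: check by simulation.** The setting was 20 clusters of 50, a binary item at 50%, no true difference, and 4,000 replicates.

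| Comparison | ICC | Weight CV | Unweighted test | Weighted counts taken as real |
|---|---|---|---|---|
| Between clusters | 0.01 | 0 | 10.7% | same |
| Between clusters | 0.05 | 0 | 29.9% | same |
| Within clusters | 0.05 | 0 | 4.8% | same |
| Within clusters | 0.05 | 0.7 | 5.3% | 11.8% |

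The first two rows agree with step 3. The last two show the limit of the problem: for a factor that varies inside networks, clustering does not inflate the error of an unweighted test, and only the misuse of weights does.

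**The case against.** The strongest reply is that the abstract says only that a chi-square will be used. It does not say Pearson, uncorrected or unweighted. A Rao-Scott test is itself a chi-square test, and a condensed article may leave the variant to an analysis plan that is not shown. This is fair, and it means one cannot say that the p-values will be wrong. What remains is that the article commits to a test and to a design that do not fit together without a correction, describes the weighting at some length, and never says that the tests use it.

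A reader might go further in three ways that the document does not support:

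- **That false-positive rates will be several times nominal.** This needs an ICC, a cluster size and a spread of weights, none of which is given. The assumed inputs above run from about nominal to nearly 30%, and some comparisons would be unaffected. Financial system may vary within networks and so be one of them.
- **That comparing all eight specialties is far worse.** With 7 df and one common deff of 1.5, the step 1 formula gives 22.7%. But specialty is itself a raking margin, so within a specialty the weights vary only by developing or developed country. An overall design effect is then not the right inflation, and the 7-df figure should not be relied on.
- **That clustering by hospital cannot be handled.** Section 2.3 does not list institution among the data collected, but that list is a summary and the draft questionnaire in the supplement is not shown.

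It is also true that simply declaring network as the sampling unit would not rescue the specialty comparison. With one network per specialty there is no replication of networks within specialty, and social-media respondents may belong to no network. The fix has to allow for this.

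**Conclusion.** The concern holds in conditional form. The article names an unqualified chi-square for data that it says will be raked and clustered by network, and it mentions no adjustment. If the test is run as an ordinary chi-square, p-values will generally be too small for comparisons between networks, and for any comparison in which weighted counts are treated as real counts.

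The size cannot be calculated from the document. For a nominal 5% test with 1 df, the true error is about 6%, 11%, 17% and 26% at assumed design effects of 1.06, 1.5, 2 and 3. It stays near 5% for an unweighted test of a factor that varies within networks. These figures assume a single multiplicative design effect.

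The point falls short of critical because the specialty and financial-system comparisons are secondary objectives.

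**What to change.** 1. **Test.** Replace the unqualified chi-square with a design-based, Rao-Scott corrected test on the raked weights, with confidence intervals from linearised or replicate-weight variances.
2. **Clustering unit.** Use a unit that crosses the comparison. Country of practice is already collected (section 2.3) and would serve for specialty. Use network only where a specialty is reached through more than one.
3. **Data.** Record the distribution route of each respondent, with a stated category for replies from social media or snowballing. Settle this before the three-month window in section 2.5 opens, because the route may not be recoverable afterwards.
4. **Limits.** Say that where a specialty is reached through a single network, specialty and network differences cannot be separated by any variance correction. Say also that the correction deals with variance and not with selection bias from convenience networks and open links.

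The cost is a few sentences of analysis wording, standard survey software and one extra field. The downside is wider intervals and fewer significant results.

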**Discussion:**

Current SSI prevention practice in UK Vascular surgery varies considerably, with little consensus on many measures. Given the inconsistency in guidelines on how to prevent SSIs, there is a need for standardization. This survey will investigate the disparity in SSI preventative measures between different surgical fields and countries.

## Introduction

1.

Over 300 million surgical procedures are performed annually worldwide (1). Up to 40% of surgical procedures are complicated by surgical site infections (SSI) (2–4). SSI rates vary by specialty, procedure, duration of the procedure and category of urgency. This variation may be due to differences in patient demographics across categories or underlying etiology of infection (5–7). Largely, SSI rates within RCTs report substantially higher incidences than nationally collected registries, owing to surveillance and diagnostic challenges within clinical practice. They are responsible for a substantial clinical burden, equating to one-third of all hospital-acquired infections (5). SSIs result in increased morbidity and mortality, with a 98% increased length of stay and a four-fold increased risk of readmission after discharge (3). Further, SSIs have a significant negative impact on the quality of life of patients, causing pain, immobility and psychological distress (8). SSIs require antimicrobial treatment, which can contribute to the development of antibiotic resistance (9). In addition, SSIs are associated with substantial healthcare costs due to protracted hospital stays, readmission, reoperation, pharmacological treatments, complex wound management systems and increased demands on staff resources (10). The true financial cost of SSI is likely to be underestimated due to wound surveillance challenges and limited access to outpatient services. However recent estimates suggest the cost to the NHS per infection is over £6103 (11).

In recent years, guidance on the prevention of SSI has been published by key organizations; National Institute for Health Care and Excellence (NICE), Centers for Disease Control and Prevention (CDC) and the World Health Organization (WHO) (12–14). However, a national survey of UK Vascular surgeons conducted by our group identified disparity in recommendations across these guidelines, which was noted to be due to the lack of underlying evidence (15). This study found variability in SSI prevention practices across different institutions, as well as a lack of relevant registries, clinical perception and literature data for SSI rates (15). This follow-on survey aims to assess the barriers in establishing uniform practice including the development of registries. As wound infections can occur after every type of surgery, wherever in the world it may take place, the steering committee of the current project decided to disseminate the follow-on survey to surgeons from all specialties internationally.

## Methods

2.

### Objectives

2.1.

Primary objective:
-To identify the barriers to establishing standardized SSI prevention practice.Secondary objectives:
-To identify intra- and inter-specialty variations in surgical site infection prevention practice.-To identify variations in practice amongst financial systems such as state and privately funded healthcare systems and economical classifications.

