### Questionnaire development

2.3.

A pilot questionnaire will be developed based on SSI prevention measures outlined in the CDC (2017), WHO (2018), NICE (2019), Wounds UK (2020) and the International Surgical Wound Complications Advisory Panel (ISWCAP) guidelines. Additionally, feedback from the survey of surgical site infection prevention practice in UK vascular surgery will be used to inform survey questions/design (12–14, 18, 19). Since the survey will be targeting participants across multiple specialties, it will only contain general prevention measures widely applicable. A draft survey will be provided in Supplementary Material 1.

The questionnaire will be structured into five sections; demographics, SSI surveillance, preoperative, peri-operative and postoperative SSI prevention domains. Data will be collected on participant surgical specialty, operative grade, country of practice and financial healthcare system of practice. SSI data will include criteria used for diagnosis. There were 15 perioperative domains formulated the UK questionnaire, which will be scrutinized against the CDC, WHO, NICE and ISWCAP guidelines outlined above by the SSC, to form a pilot questionnaire. The process of questionnaire development will be carried out through discussion by members of the SSC and a record of any question refinement will be documented. The number of questions will not be rigidly defined but the SSC will consider the impact on survey duration which can influence completion rates.

The pilot questionnaire will be distributed to at least two consultants of each surgical specialty; vascular, general, orthopedic and trauma, urology, plastic and reconstructive, cardiothoracic, neurosurgery and otolaryngology for multiple rounds of validation. After each round feedback will be analyzed by the SSC and consensus-based changes will be adopted. Any alterations will be done so on unanimous decision and documented as major (questions removed or added), and minor (wording alterations). The survey will be validated further in subsequent rounds until the SSC agrees no further alterations are required.

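### Economic class varies only between countries, but the one named test treats respondents as independent, so that comparison is anti-conservative to the extent that practice varies by country

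*Protocol article*

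**What the plan says.** Four statements in the protocol article bear on this point.

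- Section 2.1 (Objectives) lists as the second secondary objective: "To identify variations in practice amongst financial systems such as state and privately funded healthcare systems and economical classifications".
- Section 2.4 (Sample characteristics) gives the only definition of an economic class, as a weighting variable: "Socio-economic (developing vs. developed countries) variables and surgical specialties will be used to weigh the sample of responses".
- The Methods paragraph of the abstract names one test: "the chi-square test used to evaluate the impact of SSI prevention variables on responses". No clustered or design-based version is mentioned, and sections 2.1 to 2.5 name no other test.
- Section 2.3 (Questionnaire development) states: "Data will be collected on participant surgical specialty, operative grade, country of practice and financial healthcare system of practice". Country is therefore recorded, but the article nowhere uses it as a cluster, stratum or unit of analysis.

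Section 2.4 does mention clusters, but for sampling: "Each network of distribution will provide a cluster, i.e., VERN for the vascular surgeons and PIACO group for general surgery". It also states: "Given the global nature of the survey, no sample size will be calculated".

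**The concern.** A label attached to countries cannot vary among surgeons within one country. The information on whether the two economic classes differ therefore comes from how many countries each class contains and how much those countries differ. Adding surgeons from a country already in the sample helps much less than the respondent count suggests. An ordinary chi-square credits each surgeon as an independent observation. That is right only if two surgeons in the same country are no more alike in practice than two surgeons from different countries of the same class.

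The article does not expect that. Its Discussion presents the survey as a study of disparity between countries as well as between surgical fields. Its Limitations section (3.1) anticipates differing local and national guidelines, unequal access to resources and uneven response by country.

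What is at stake is attribution. A few countries that respond heavily and happen to share a habit could produce a significant class difference that reflects those countries rather than economic class. Section 2.4 intends the results to be extrapolated to wider populations, so such a difference would be carried further than the data allow.

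**Working it through.** **Inputs.** The article gives no significance level, sample size, number of countries, respondents per country or ICC, so it has no figure to reproduce. All of the following are assumptions:

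- two-sided 5% level
- no true class difference
- a yes/no practice item with 50% prevalence
- *m* respondents per country
- within-country ICC *ρ* between 0 and 0.20

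**Formula.** With equal country sizes, the variance of a class proportion is the binomial variance multiplied by the design effect DE = 1 + (*m* − 1)*ρ*. The chi-square uses only the binomial part. Under the null its signed root has standard deviation √DE instead of 1, so

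actual type I error = 2 × [1 − Φ(1.96 / √DE)].

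**Numbers put in:**

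- *m* = 20, *ρ* = 0.01: DE = 1 + 19 × 0.01 = 1.19; 1.96/√1.19 = 1.80; error 7.2%.
- *m* = 20, *ρ* = 0.10: DE = 1 + 19 × 0.10 = 2.90; 1.96/√2.90 = 1.15; error 25.0%.
- *m* = 50, *ρ* = 0.01: DE = 1 + 49 × 0.01 = 1.49; 1.96/√1.49 = 1.61; error 10.8%.
- *m* = 50, *ρ* = 0.10: DE = 1 + 49 × 0.10 = 5.90; 1.96/√5.90 = 0.81; error 42.0%.

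**Wider grid (type I error at nominal 5%, equal country sizes):**

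| Respondents per country | ICC 0 | 0.01 | 0.05 | 0.10 | 0.20 |
|---|---|---|---|---|---|
| 5 | 5.0% | 5.5% | 7.4% | 9.8% | 14.4% |
| 10 | 5.0% | 6.0% | 10.4% | 15.5% | 24.1% |
| 20 | 5.0% | 7.2% | 16.0% | 25.0% | 37.1% |
| 50 | 5.0% | 10.8% | 29.1% | 42.0% | 55.1% |
| 100 | 5.0% | 16.5% | 42.2% | 55.3% | 66.7% |

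**Simulation check.** Beta-binomial country effects, 20,000 replicates per scenario, Pearson chi-square without continuity correction, and either equal or lognormal country sizes:

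| Countries per class | Mean per country | ICC | Equal sizes | Unequal sizes |
|---|---|---|---|---|
| 20 + 20 | 25 | 0.05 | 19.7% | 30.5% |
| 15 + 35 | 20 | 0.01 | 7.4% | 9.9% |
| 15 + 35 | 20 | 0.10 | 25.5% | 38.8% |
| 25 + 25 | 50 | 0.05 | 29.9% | 43.8% |

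The first row can be compared with the formula: DE = 1 + 24 × 0.05 = 2.20; 1.96/√2.20 = 1.32; error about 18.6%. The equal-size columns agree with the formula. In these rows unequal sizes make matters worse, because a few large countries dominate their class.

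**With country as the unit.** In the same simulations a Welch t-test on country proportions gave 4.2% to 5.3% in every scenario (ICC 0 to 0.20, 20 to 50 countries, equal or unequal sizes).

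**Do the stated devices repair it?** Section 2.4 says "Raking will be used to assign weight values to each survey respondent in such a manner" that margins are matched. Matching margins for class and specialty changes how much each respondent counts. It neither balances the mix of countries within a class nor corrects the variance for within-country correlation. The network clusters are named for sampling, and the two examples are identified by specialty. Nothing says that they enter the analysis or stand in for country.

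**The case against.** The strongest reply is that the link between test and objective is inferred. The chi-square appears once, in an abstract, in a sentence that does not mention economic class. With cluster sampling and raked weights, a design-based chi-square would be a natural choice, and a condensed article may leave the variance estimator to a fuller plan. This limits how firmly the point can be put. It does not remove it: the test as written is the plain one, no other is offered, and it does not suit a factor that the article itself defines at country level.

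Second, if the target is surgeons in the actual set of countries, country effects are part of the real class difference rather than noise. That would carry weight if the mix of countries within each class were fixed by design. Here it results from voluntary response through societies, social media and snowballing, and raking balances only class and specialty.

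Third, the abstract and section 2.5 describe dissemination through national societies and membership organisations. Some networks may therefore sit within one country, and clustering on them would absorb part of the correlation. This stands: the article does not give the geographic span of the networks, so no figure for a network-clustered analysis can be supported.

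Fourth, funding system is asked of each respondent and can vary within a country. This also stands, and it limits the point to economic class, plus funding only where a country has a single system.

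Finally, section 3.1 expects regional discrepancies to be small because the questions rest on international guidelines. That concerns what is asked, not whether practice is uniform across countries.

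**Conclusion.** The point holds in conditional form. For the economic-class part of one secondary objective, the named test ignores within-country correlation, and nothing else in the article is stated to account for it. The test is anti-conservative at any positive ICC with more than one respondent per country. Under the assumptions shown (5% level, equal country sizes, ICC 0.01 to 0.10, 20 to 50 respondents per country) the type I error is roughly 7% to 42%, and the simulated scenarios with unequal sizes gave higher values.

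A reader might infer that false positives will occur far more often than 5% of the time whatever the data look like. The article does not support that. It gives none of the quantities that fix the size, and with 5 respondents per country and an ICC of 0.01 the error is only 5.5%. At the other end, 100 per country and an ICC of 0.20 give about 67%. Nor should the point be extended to the whole financial-systems objective or to the primary objective. It deserves correction because the article's own premise is that practice differs between countries, and because the remedy needs no new data.

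**What to change.** For the economic-class contrast, and for funding system only where it is fixed by country, replace the plain chi-square with an analysis that treats country as the cluster. Two suitable choices are:

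- a logistic mixed model with a random intercept for country
- a design-based (Rao-Scott) test on the raked weights with country as the cluster

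The second stays closer to the surgeon-level weighting in section 2.4. An unweighted comparison of country proportions held its level in the simulations, but it gives a small country the same weight as a large one and so answers a somewhat different question. The mixed model and the Rao-Scott test were not themselves simulated here.

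Whichever is chosen, base the degrees of freedom on the number of countries, and report the number of countries and of respondents in each class. State the significance level as well, so that the error rate has a reference.

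The cost is a sentence or two in the analysis description and a modest amount of extra analysis. Country of practice is already on the questionnaire. The real downside is wider intervals for this contrast, and they may be very wide if one class is represented by few countries.
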